#### Aim 3: Intervention Feasibility and Preliminary Efficacy Evaluation Study

##### RCT Design

The intervention modules will be tested through an RCT design using mixed methods in 70 young adults who engage in NMUPO [93]. The primary purpose is to determine acceptability, usability, feasibility, and initial efficacy. Participants reached by peer leaders or advertisements on social media will be navigated to a screening survey on REDCap and scheduling a meeting with the research team for informed consent. Participants will be required to comply with the user safety agreement. Participants will be randomly assigned to the parallel intervention (35/70, 50%) or control group (35/70, 50%) using computer-generated random numbers. Participants are blinded to the randomized assignments. Intervention group will be guided to join Instagram peer-led private groups (n=10-15 each). Participants will be asked to provide their Instagram accounts to their assigned peer leaders for participating in intervention activities. Peer leaders will set up private and independent groups via their Instagram accounts and will send direct invitations to their assigned participants to join groups. Once group membership is confirmed, peer leaders will post intervention materials and lead group activities according to the plan as developed in aim 2. Private groups will synchronously deliver intervention packages over 12 weeks. To ensure confidentiality, participants will be assigned unique study IDs, which will be used for data collection and intervention activities. The intervention group will participate in data collection through multiple formats, including Instagram paradata, pre- and postintervention surveys, EMA surveys, and postintervention semistructured interviews.

The control group will not engage in any intervention activities but will complete the pre- and postintervention surveys.

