##### Web-Based Pre- and Postintervention Surveys

The web-based pre- and postintervention surveys will be developed and administered on REDCap [94] to measure demographic variables as well as psychosocial and behavioral factors outlined in the IMB-based conceptual framework. Factors include NMUPO behaviors (past–3-month NMUPO) and information- and motivation-related factors (ie, NMUPO knowledge, NMUPO risk perception, outcome expectancies, self-efficacy, psychological distress, resilience, and other substance use). Web-based surveys will be conducted among participants in both the intervention and control groups. Participants will receive survey links via inbox messages to the Instagram accounts they provide for the study. The preintervention survey will be sent 2 weeks before the intervention (baseline), and the postintervention survey will be sent in the week immediately following the intervention (12-week follow-up). The survey will be self-administered and take approximately 20 to 30 minutes to complete. If participants cannot complete the surveys at one time, they can save their responses, and the platform will generate a code that allows them to resume the survey within the same week. The survey will also provide forward and back buttons, allowing participants to review and change their responses before they submit their surveys. Study IDs and filling time will be collected for determining duplicate entries. e-gift cards will be provided for the completion of surveys (baseline and 12 weeks; US $30 each).

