### Project Timeline

A detailed study timeline is shown in Table 1.

**Table 1 table1:** The project timeline.

		Year 1	Year 2	Year 3	Year 4	Year 5
**Phase 1: formative study (aim 1)**		✓	✓			
	Literature review and assessment development (ie, surveys and semistructured interviews)	✓				
	IRB^a^ submission	✓				
	Peer leader recruitment, participant recruitment and assessment, and community advisory board establishment	✓				
	Transcription and data analysis or extraction		✓			
**Phase 2: intervention development (aim 2)**			✓	✓		
	Development of multimedia files or features based on data from formative research		✓			
	Establishment of IMB^b^-based intervention module packages		✓	✓		
	Development of prototype for social media groups and pages (ie, Instagram [Meta Platforms, Inc])			✓		
	Peer leaders’ and administrators’ training (doctoral clinical psychology trainees)			✓		
**Phase 3: intervention feasibility and preliminary efficacy evaluation study (aim 3)**				✓	✓	
	Participant recruitment, preintervention assessment, and randomized controlled trial assignment			✓		
	Delivery of intervention			✓		
	EMA^c^ surveys and paradata collection			✓		
	Postintervention assessment and interviews				✓	
	Data analysis				✓	
	Revisions based on participants’ feedback				✓	
	Dissemination and disclosure of research findings				✓	✓
	Preparation and submission a research proposal for a large-scale intervention effectiveness evaluation with a randomized controlled trial design				✓	✓

^a^IRB: institutional review board.

^b^IMB: information-motivation-behavioral skills.

^c^EMA: ecological momentary assessment.

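### The article does not settle whether the baseline survey precedes allocation, so self-reported baseline could be answered once the arm can be inferred; the synchronous start would allow baseline first, then one stratified batch

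*Protocol article*

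**What the plan says.** All references are to the protocol article.

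- **RCT Design.** People reached by peers or advertisements "will be navigated to a screening survey on REDCap and scheduling a meeting with the research team for informed consent". Allocation comes next in the narrative: "Participants will be randomly assigned to the parallel intervention (35/70, 50%) or control group (35/70, 50%) using computer-generated random numbers". Intervention participants then give their Instagram accounts to the peer leaders they have been assigned to, and are invited into private groups. Delivery has a common calendar: "Private groups will synchronously deliver intervention packages over 12 weeks". The control group has no intervention activities but "will complete the pre- and postintervention surveys". The section also states: "Participants are blinded to the randomized assignments".
- **Web-Based Pre- and Postintervention Surveys.** "The preintervention survey will be sent 2 weeks before the intervention (baseline"). Links go to the Instagram accounts that participants supply. On recipients: "Web-based surveys will be conducted among participants in both the intervention and control groups". Allocation is not mentioned as a reference point.
- **Project Timeline, Table 1.** One row reads "Participant recruitment, preintervention assessment, and randomized controlled trial assignment", with assessment ahead of assignment.
- **Multivariate Analyses.** Outcomes at baseline and 12 weeks go into a repeated measures analysis of covariance, with demographics as the named covariates.
- **Participants and Recruitment.** Stratification is mentioned for recruitment, on demographics. Past 3-month NMUPO is already asked at prescreening. No stratification of the allocation is stated.

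**The concern.** The control arm gets nothing and the intervention arm is invited into a peer-led group. The blinding statement therefore cannot hold once invitations go out. A participant who completes the baseline survey after that point can infer the arm.

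The survey outcomes are self-reported, and the limitations in the Discussion accept that social desirability may affect them. Baseline is one of only two analysed time points, so a baseline shifted by knowledge of the arm would pass directly into the contrast between arms over time. Unlike chance imbalance, that would be a systematic error.

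The second, smaller issue is a missed opportunity. Everyone starts together and NMUPO frequency is collected before the start. The trial could therefore balance the arms on its main behavioural measure at almost no cost, and the article does not say that it will.

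**Working it through.** **1. Order of steps, side by side**

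| Section | Order or timing given |
|---|---|
| RCT Design | screening, consent, assignment; accounts then given to assigned peer leaders; surveys listed afterwards by arm |
| Web-Based Pre- and Postintervention Surveys | baseline two weeks before intervention start, sent to Instagram accounts; not tied to allocation |
| Project Timeline, Table 1 | recruitment, preintervention assessment, assignment |

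The survey section fits either order. RCT Design leans towards assignment first, because the only account-collection step it describes for the trial follows assignment. Table 1 gives baseline first. The Results section puts the start of trial recruitment in late 2027 and the intervention in early 2028, so there may be weeks or months between consent and baseline. No section says that baseline must be returned before the arm is disclosed.

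**2. Chance imbalance at exactly 35 per arm**

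The plan states no imbalance figure to reproduce. Inputs are n = 35 per arm (RCT Design), effect sizes of 0.17 and 0.34 in absolute value, and retention of 75% to 93% (both Power Analysis).

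SD of the standardised baseline difference = √(2/n) = √(2/35) = 0.239.

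- P(|difference| > 0.34): z = 0.34/0.239 = 1.42, two-sided probability 15.5%.
- P(|difference| > 0.17): z = 0.17/0.239 = 0.71, two-sided probability 47.7%.

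At the lowest quoted retention, 0.75 × 35 ≈ 26 per arm. The SD becomes √(2/26) = 0.277 and the two probabilities 22.0% and 54.0%.

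For a two-level NMUPO factor, such as more frequent versus less frequent use, the article gives no prevalence. Assuming 20% to 50% and a fixed 35/35 split (hypergeometric), the chance that the arms differ by 20 percentage points or more lies between 3.4% and 15.1%.

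**3. What the imbalance costs**

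- *Baseline as a linear covariate.* The variance of the treatment effect is inflated by 1/(1 − r²), where r is the correlation of arm with baseline. Over 20,000 simulated 35/35 allocations the mean inflation is 1.5% and the 95th percentile 5.8%.
- *Contrast of change from baseline.* A chance imbalance D shifts the expected contrast by (1 − ρ) × D in size, taking equal SDs at both times. The pre-post correlation ρ is not stated. With D = 0.34, the shift is 0.5 × 0.34 = 0.17 SD at an assumed ρ of 0.5, and 0.3 × 0.34 = 0.10 SD at 0.7.

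The penalty therefore depends on whether the baseline value itself is adjusted for. The article names only demographics.

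**The case against.** The strongest reply is that Table 1 already gives the recommended order. RCT Design never says that baseline follows assignment, and its later list of surveys by arm can be read as data sources and not a chronology. The flowchart (Figure 2) is not shown and may settle the matter. All of this stands. A reader might infer that the plan randomises before baseline, but the documents support only that the order is left open.

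A reader might also take the reference to random numbers as unrestricted, coin-type allocation that would not deliver 35/35. The text does not support this. Aim 3 and RCT Design fix a 1:1 ratio and 35 of 70 in each arm, and computer-generated numbers are equally the basis of a restricted list. A condensed article may also leave sequence and stratification details to the full protocol, so their absence is not an error in itself.

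Nor can one say how many randomised people would lack a baseline. The documents give no figure for baseline non-return, and Bivariate Analyses provides for multiple imputation.

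On blinding, participants could be unaware of their arm until invitations are sent, even if a list already existed. That is correct, and it is why disclosure of the arm is the step to fix relative to baseline. Finally, efficacy is secondary in this pilot. The EMA, paradata and interview data behind the primary outcomes come from the intervention arm, so balance between arms does not affect them.

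**Conclusion.** The point holds in limited form. The article's sections do not give one order for baseline and allocation. One literal reading allows self-reported baseline to be answered after the arm can be inferred, in a measure that enters the efficacy model directly. This is a possible bias whose size cannot be estimated from the documents, and it is not shown to occur. It is the main reason to act.

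The balance issue is secondary. At 35 per arm, baseline differences as large as the quoted effects are fairly likely by chance (about 15% for 0.34 SD, 48% for 0.17 SD). They are not bias, and cost on average about 1.5% in variance once baseline is a linear covariate. They matter more in a change contrast without that adjustment. The probabilities assume an unstratified 35/35 split and a roughly normal mean difference. The change-contrast figures also rest on an assumed correlation of 0.5 to 0.7.

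**What to change.** Bring RCT Design and the survey section into line with Table 1 by stating one sequence: consent, baseline survey returned, then assignment disclosed. Say when Instagram accounts are collected from both arms, so that baseline links do not depend on assignment to a peer leader.

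Because delivery is synchronous, allocate all baseline responders in one 1:1 batch shortly before the start, stratified on baseline NMUPO frequency. Include that baseline value in the efficacy model alongside the demographics.

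The cost is some wording and a stratified list. The one practical downside is that baseline return, allocation and group set-up must all fit within the two-week window. The Results section says that the aim 3 protocol goes for ethics review in early 2027, so the change can be made before the trial is submitted.

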##### Web-Based Pre- and Postintervention Surveys

The web-based pre- and postintervention surveys will be developed and administered on REDCap [94] to measure demographic variables as well as psychosocial and behavioral factors outlined in the IMB-based conceptual framework. Factors include NMUPO behaviors (past–3-month NMUPO) and information- and motivation-related factors (ie, NMUPO knowledge, NMUPO risk perception, outcome expectancies, self-efficacy, psychological distress, resilience, and other substance use). Web-based surveys will be conducted among participants in both the intervention and control groups. Participants will receive survey links via inbox messages to the Instagram accounts they provide for the study. The preintervention survey will be sent 2 weeks before the intervention (baseline), and the postintervention survey will be sent in the week immediately following the intervention (12-week follow-up). The survey will be self-administered and take approximately 20 to 30 minutes to complete. If participants cannot complete the surveys at one time, they can save their responses, and the platform will generate a code that allows them to resume the survey within the same week. The survey will also provide forward and back buttons, allowing participants to review and change their responses before they submit their surveys. Study IDs and filling time will be collected for determining duplicate entries. e-gift cards will be provided for the completion of surveys (baseline and 12 weeks; US $30 each).

##### Use of EMA

EMA will be used through brief evening surveys to screen the prompt acceptability and usability (the Usefulness, Satisfaction, and Ease of use questionnaire) [95] and the dose of particular modules in the intervention group. The EMA survey will be conducted once every 2 days during the intervention. The daily EMA is widely used in behavioral trials [39]. Data will be collected via a 20-second survey on a smartphone app (ExpiWell), which is user-friendly and customizable for EMA development and implementation [96]. A prompt will be sent at the moment for assessment and tailored for the intervention materials in the past 2 days. A reminder will be provided if no response is made in 30 minutes. For safety purposes, if an EMA occurs during an incompatible activity (eg, driving), participants will be instructed to ignore or postpone the prompt.

##### Postintervention Semistructured Interviews

At week 12, participants will join semistructured interviews measuring (1) feasibility, usability, and acceptability and (2) reactions to the content, format, concepts, visual presentation, assessments (survey and EMA) and adaptation to other platforms. The interview guide will be based on mobile health (mHealth) studies [97]. The interview will be audio recorded and take approximately 60 minutes via an online meeting application (eg, Zoom).

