### Measures

#### Mixed Methods Measures for Primary Outcomes: Intervention Feasibility Outcomes

Multiple forms of data will be collected within 12 weeks during the intervention for the intervention feasibility evaluation.

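### The timing labels let the intervention-arm-only interview come before the outcome survey, and nothing in the plan rules that order out

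*Protocol article*

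**What the plan says.** The interview is timed in Postintervention Semistructured Interviews: "At week 12, participants will join semistructured interviews measuring (1) feasibility, usability, and acceptability". The same timing is repeated under Feasibility, Acceptability, and Usability. On length and mode: "The interview will be audio recorded and take approximately 60 minutes via an online meeting application". Besides feasibility, usability and acceptability, it covers "reactions to the content, format, concepts, visual presentation, assessments (survey and EMA) and adaptation to other platforms".

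RCT Design lists the interview among the intervention group's data sources, ending "surveys, EMA surveys, and postintervention semistructured interviews". For the other arm it says: "The control group will not engage in any intervention activities but will complete the pre- and postintervention surveys".

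The outcome survey is timed in Web-Based Pre- and Postintervention Surveys: "the postintervention survey will be sent in the week immediately following the intervention (12-week follow-up". The same section gives its payment time points as "baseline and 12 weeks; US $30 each". The survey is self-administered on the web and carries NMUPO, knowledge, risk perception, expectancies, self-efficacy, distress, resilience and other substance use.

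Two further statements bear on timing. The opening of Mixed Methods Measures for Primary Outcomes, the part of Measures that contains the interview, says: "Multiple forms of data will be collected within 12 weeks during the intervention for the intervention feasibility evaluation". Table 1 puts the postintervention assessment and the interviews together in one Year 4 row, apart from delivery, EMA and paradata in Year 3.

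**The concern.** The interview is a measurement procedure that one arm has and the other does not. The treatment comparison rests on self-report, and the limitations paragraph of the Discussion itself names social desirability and recall bias as threats to such measures. If intervention participants spend about an hour discussing how acceptable and useful the programme was, and how they found its assessments, and then complete the outcome survey, their answers could shift. Controls answer the same survey without that conversation.

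Where every intervention participant and no control is interviewed first, exposure to the interview coincides with arm. No analysis could then separate a shift caused by the interview from an effect of the intervention. The preliminary efficacy results are meant to inform a larger trial, so an avoidable measurement difference between the arms should not be left in. The risk comes only from the order of two procedures, and the sponsor controls that order.

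**Working it through.** The plan gives no figure to reproduce here. The check sets the timing statements side by side.

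**Literal week count**
- The intervention lasts 12 weeks (Intervention Components, Overview), so it occupies weeks 1 to 12.
- The interview is at week 12. The opening of Mixed Methods Measures for Primary Outcomes supports this by placing feasibility data inside the intervention period.
- The survey goes out in the week after the intervention: 12 + 1 = week 13.
- Result: interview first, survey second.

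**Statements that allow another order**
- The survey is also called a 12-week follow-up and is paid as a 12-week assessment. On that label it shares the interview's time point.
- The interview is described as postintervention in RCT Design, in its own section heading and in Qualitative Analyses. That sits badly with a date inside week 12.
- Table 1 places the interviews after delivery, in the same row as the postintervention assessment, and gives no order within the row.
- The interview asks for reactions to the survey. That would fit a survey already completed, but the baseline survey could be what is meant.
- Result: the two may fall together or in either order.

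**What is fixed**

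| Item | Intervention arm | Control arm |
|---|---|---|
| Planned size | 35 | 35 |
| Postintervention survey | yes | yes |
| Interview of about 60 minutes | yes | no |
| Survey required before interview | not stated | not applicable |

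Exposure, if the interview comes first: up to 35 of 35 against 0 of 35. The article gives no number to be interviewed, so 35 is an upper limit.

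**Scale of contact**
- The Peer Support Module schedules a weekly 30-minute live group: 12 × 30 = 360 minutes.
- Interview relative to that: 60 / 360 = 0.17, about 17% on top.
- EMA prompts every 2 days: (12 × 7) / 2 = 42 prompts, also asking about usability and acceptability.
- Controls have none of these.

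The contact figures describe exposure, not bias. Nothing in the document allows a shift in the outcome scores to be calculated from them.

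**The case against.** The strongest objection is that the order is not stated. A reader might infer from weeks 12 and 13 that the interview definitely precedes the survey, and that one arm's outcomes are therefore primed. The document does not support that. It gives the survey a 12-week label as well, calls the interview postintervention, and groups the two after delivery in Table 1. A reader might also infer that the interview takes place before the last content has been delivered; that is not stated either. This part of the objection stands, and the point is worded accordingly.

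It also stands that priming is a possibility and has not been shown. The interview concerns the programme and its assessments, not opioid use, distress or resilience directly. The survey is completed alone on the web. The article does not say who conducts the Aim 3 interview, so contact with study staff is an assumption. The affected outcomes are secondary, and the trial is a pilot whose primary outcomes are feasibility, usability and acceptability.

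Two arguments carry less weight. The first is that an hour is small beside 360 minutes of group contact and 42 prompts. The groups, however, are part of the treatment under test, so what they change belongs to its effect, while a shift caused by the interview would be a measurement artefact. The comparison does show that the added exposure is modest. The second is that a journal article may leave the order of end-of-study procedures to the full protocol. Here the article does state the timing, in several places, and the statements disagree.

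**Conclusion.** The point holds in a limited form. Only the intervention arm is interviewed. The literal labels put the interview before the outcome survey, other statements allow the reverse or a shared time point, and no rule prevents the interview from coming first. Some participants could be interviewed before the survey and others after it.

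If the interview does come first, response bias in one arm is possible on the secondary self-reported outcomes. The extent of exposure is known (up to 35 against 0), but the size and even the presence of a shift are not. The conclusion rests on two assumptions: that the interview is held with most or all intervention participants, and that discussing the programme and its assessments can influence later self-report. The feasibility outcomes are not threatened in this way. The change is worth making because the same rule settles the matter under either reading, at little cost.

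**What to change.** 1. In Postintervention Semistructured Interviews and in Feasibility, Acceptability, and Usability, replace the week 12 timing with a rule: the interview is held only after the participant's postintervention survey has been submitted, or after its one-week window has closed. The survey section already lets participants resume a saved survey within the same week, so a one-week window fits the existing procedure.
2. In Web-Based Pre- and Postintervention Surveys, state that the postintervention survey goes to both arms in the same calendar week, and use one label for that time point.
3. In the opening of Mixed Methods Measures for Primary Outcomes, exempt the interview from the statement that feasibility data are collected during the intervention, so that it agrees with the postintervention heading and Table 1.

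The cost is a few sentences. Interviews move about one to two weeks later, with slightly longer recall of the programme. According to Results, the Aim 3 protocol goes for ethics review in early 2027 and trial recruitment starts in late 2027, so the change can be made before any participant is randomised.
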